#### Fox Insight App

The Fox Insight app is an Android/iPhone app created and developed by Intel Corporation (Tel Aviv, Israel). This app receives 50 accelerometer data points per second from the Pebble smartwatch, and estimates levels of activity, tremor, and sleep movement analyses using dedicated algorithms running within the app. The app presents these estimated quantities to the user by means of graphs and summary reports of the data collected.

Activity graphs show the level of activity throughout the day (Figure 1). The calculation is performed by aggregations (30 second intervals) of the raw data previously collected. The graph also highlights the moments in time when medication was taken. Daily tremor graphs show how many minutes the patient has experienced tremor during a certain day (a tremor is defined as any movement in the range of 3.5-12Hz). Sleep analysis graphs (Figure 2) show the amount of time that the patient has been active during the sleep time. These graphs provide an impression of the intensity and duration of movements.

These estimated quantities are sent every 10 minutes to a cloud-based data platform through an Internet connection on the smartphone. Different mechanisms allow the participants to know whether the data are recorded correctly. First, participants can check the metric graphs (eg, activity graph, sleep analysis, and tremor); these graphs are plotted using the data recorded in the servers, and will only appear if the data were collected. Second, the main app screen (Figure 3) displays how many hours of data the participant has contributed to the study; if this metric does not increase it means the data are not being collected. Finally, participants can view the white *pill* icon in the smartphone task bar; if the icon has a crossing line over it, data are not being actively recorded.

**Figure 1 figure1:**
[figure not shown]
Fox Insight Mobile App activity graph.

**Figure 2 figure2:**
[figure not shown]
Fox Insight Mobile App sleep analysis graph.

**Figure 3 figure3:**
[figure not shown]
Fox Insight Mobile app main screen.

#### Fall Detector

Falls and movement patterns are measured with a pendant device. Patients are given the choice to wear either a fall detector (FD), or the Philips Mobility Monitor (PMM) [22,23]. Both sensors are CE-marked non-medical devices; the PMM is developed by Philips Research. The FD device used in this study is an adapted fall detection device, originally intended for seniors living in their own homes, that was designed to detect falls from stance. The FD device can be worn 24/7, while the PMM is recharged overnight and thus only worn during the day.

The FD device uses multiple sensors and a proprietary analytical algorithm to detect some types of fall events, which are stored in the device. The PMM contains a 3-axial accelerometer and a barometric pressure sensor, with a sampling frequency of 50Hz and 25Hz, respectively. Data are continuously recorded and stored on a micro SD card within the device. Based on these data, information about the daily movements, as well as falls detected, are calculated after read-out at the end of each patient’s trial period.

### Wearable Sensors Phase Two

Devices will be chosen after analysis of the study procedure, and data collection is complete in phase one.

### Technical Support

Patients will have access to extended support, including an installation guide, user manual, and information on the study’s webpage. For the duration of the study, a helpline will be available during working hours to support the installation and device usage, and for troubleshooting.

### Clinical and Feasibility Assessment

Certified physiotherapists will perform the short version of the Parkinson Progression Marker Initiative (PPMI) in order to assess disease status [24]. This assessment includes: the MDS-UPDRS (parts I, III, and IV) for disease rating [8]; the Montreal Cognitive Assessment for cognition [25]; and the Modified Schwab and England Activities of Daily Living Scale for activities of daily living [26].

Additional questionnaires will be completed by the patients: MDS-UPDRS part II for motor experiences of daily living; the Scales for Outcomes in Parkinson’s Disease - Autonomic System (SCOPA-AUT) for autonomic dysfunction [27]; the Geriatric Depression Scale for depressive symptoms [28]; and the Epworth Sleepiness Scale for day sleepiness [29].

To assess feasibility, patients will also complete the System Usability Scale [30] and a satisfaction survey created by the research team, to address patients’ impressions on how well particular features of the app are functioning, and the burden associated with the methodology. An overview of outcomes is provided in Multimedia Appendix 2.

### Data Collection and Management

Due to privacy issues, patients will receive a personal identification code that does not contain any information that relates to the individual. The key-file, connecting personal identification codes to personal information, will be stored on a Radboudumc data server, and only the research team has access to the key-file. The key-file will be stored on a different server from the study data for five years, allowing the research team to contact patients after they have finished the study. We anticipate that our efforts to obtain additional research funding will allow for additional follow-up assessments. The key-file will be destroyed after five years.

Data for the study will be collected in the following ways:

*Data from smartwatch and smartphone*: data will be collected continuously in a coded manner, and will be transferred to Intel’s cloud data storage environment using an Internet connection. The cloud environment is based on Amazon Web Services, and developed and managed by Intel’s Advanced Analytics team. Data from the watch and Fox Insight app will be transferred to the Intel platform using a personal identification code for each patient. Moreover, no personally identifiable data will be entered into the app or sent to this data storage platform.

*Data from the PMM and FD*: data will be collected during the time that patients are not lying in bed. Each FD has a unique identifier, and Philips Research will only receive coded data. No personal information is required to use these devices, and no personal data from patients will be shared with Philips.

*Data from the clinical assessments:* data will be collected by means of paper-based forms, and will be entered manually into an online certified data management system. Forms will only contain personal identification codes.

*Data from support and logistics*: ZenDesk software will be used to support the logistics of the recruitment process, and provide technical support during the follow-up phase. ZenDesk is Internet-based, and data access is authenticated by username and password. All communications with ZenDesk servers use industry-standard Secure Sockets Layer encryption by default, and the ZenDesk servers are located at a different site than the Amazon servers. Therefore, research data is never stored on the same server as patients’ identifying codes.

Patients that complete the clinical assessment and stream data for more than seven days will have their data included in further analyses.

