To overcome these limitations, wearable sensors are emerging as new tools to continuously and longitudinally obtain information from patients in real-life. The accuracy of sensor data for everyday activity recognition (eg, walking, running) in real-life ranges from 58% to 97% [11]. These sensors, typically consisting of embedded accelerometers, have been used successfully to determine PD-related symptoms [12-16]. However, to date these studies have relied upon small sample sizes (n=5 to 43 participants) and short follow-up periods (3 days to 6 months; see Multimedia Appendix 1).

The primary aim of the Parkinson@Home study is to evaluate the feasibility and patient compliance of using wearable sensors to collect data for at least 3 months in a large patient group. A secondary aim of this study is to address the usability of these data for answering clinically relevant research questions (eg, to determine the relationship between sensor-derived measures and clinical measures). Finally, the study aims to build a database for future development and testing of novel algorithms applied to sensor-derived data from PD patients during daily functioning.

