## Methods

### Study Design

The Parkinson@Home study is an observational study involving 1000 patients (from whom data will be recorded) and 250 physiotherapists (who will assist in performing the clinical assessments, and who may act as personal coaches during follow-up). Both patients and therapists will be recruited throughout the Netherlands. The study consists of two phases. Phase one aims to assess the feasibility of deploying wearable sensors in a large PD population (n=300). For this purpose, patients will use a number of wearable devices (Pebble smartwatch, Android smartphone, and fall detector) in combination with a customized app (Fox Insight). Follow-up will occur after 3 months (13 weeks), starting from the moment the first data are streamed to the server. In addition to using wearable devices, participants will attend a one-time consultation, during which a detailed clinical assessment will be performed by an experienced physiotherapist or a research team member. This clinical assessment will take place in week 7, or later during the follow-up period. Phase two, which will include an additional 700 participants, aims to collect raw sensor data in order to investigate the usability of these data for answering clinical research questions. This phase will also be used to build a database for future validation of novel algorithms applied to sensor-derived data from PD patients during daily functioning. Patients involved in phase one can also be included in phase two if they wish. Data collection for clinical results and device-based outcomes, as well as the follow-up period, will be identical to phase one. To ensure the success of the raw data collection during phase two, devices and raw data collection strategies used in this phase will be chosen after the evaluation of data collected during phase one.

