### Data Analyses

#### Phase One

Feasibility and compliance will be addressed using descriptive analyses. For feasibility, the primary outcomes will include the total support time per participant, the number and rate of drop-outs, usability of the system, bias within recruitment strategies, and the type of problems faced by patients. Regarding compliance, the outcome measures include the total hours of sensor data collected per participant, the number of compliant days, and the percentage of time that sensor data were streamed during the follow-up period.

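### Applied as written, the rule for entering further analyses selects on retention and streaming, so it inflates phase-one compliance and conflicts with counting drop-outs

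*Protocol article*

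**What the plan says.** The entry rule closes the section Data Collection and Management, directly before Data Analyses: "Patients that complete the clinical assessment and stream data for more than seven days will have their data included in further analyses". It names no phase and makes no exception.

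Study Design fixes when the assessment can happen: "This clinical assessment will take place in week 7, or later during the follow-up period". It also sets the clock: "Follow-up will occur after 3 months (13 weeks), starting from the moment the first data are streamed to the server".

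The Introduction gives the primary aim: "evaluate the feasibility and patient compliance of using wearable sensors to collect data for at least 3 months in a large patient group". Data Analyses, Phase One, turns this into outcomes. For feasibility, "the primary outcomes will include the total support time per participant, the number and rate of drop-outs, usability of the system", followed by recruitment bias and the types of problem patients met. For compliance, "the total hours of sensor data collected per participant, the number of compliant days, and the percentage of time that sensor data were streamed", the last taken over the follow-up period. The analysis is descriptive, and the section names no denominator of its own.

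Study Design adds that the phase-two devices and raw-data strategy will be chosen after the phase-one data have been evaluated.

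**The concern.** The rule has two conditions, and each removes patients because of how they did on a phase-one outcome. Requiring an assessment in week 7 or later removes everyone who leaves earlier. Requiring more than seven days of streaming removes the worst streamers directly. A compliance figure computed on the rest describes people who stayed and streamed, whereas the aim is to learn how a large patient group copes with the devices for at least three months.

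The rule also cannot be squared with the drop-out outcome. A drop-out rate taken in a set that requires staying to week 7 misses the early drop-outs by construction.

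The clock adds a smaller gap. Follow-up is counted "starting from the moment the first data are streamed to the server", so an included patient who never gets the devices working has no follow-up period and no percentage of time streamed.

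At stake is the headline compliance result, which feeds the choice of devices and data collection for the 700 further patients of phase two.

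**Working it through.** **1. The document's own figures.** Results, Patient Recruitment Process, reports 300 inclusions from 342 invited: 300/342 = 87.7%, as stated. The columns of Table 1 sum to 1164 applicants and 258 participants, as stated. No sample size or precision calculation is given for phase one, so there is none to reproduce.

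**2. Ceilings for excluded patients.** Follow-up is 13 × 7 = 91 days. Taking percentage of time streamed over the full 91 days:
- excluded for streaming at most 7 days: at most 7/91 = 7.7%;
- left before week 7, so at most 6 × 7 = 42 days: at most 42/91 = 46.2%.

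Removing such patients raises the mean whenever the retained mean lies above these ceilings.

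**3. Size of the effect.** Let d be the share excluded, c the mean compliance of those retained and e the mean compliance of those excluded.
- Mean over all included = (1 − d)·c + d·e
- Overstatement = c − [(1 − d)·c + d·e] = d·(c − e)

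The document gives none of these three. For illustration c = 88%, borrowed from the pilot described in Study Design (20 patients, four weeks), and d = 5%, 10% or 20%.

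| Excluded patients | e | d = 5% | d = 10% | d = 20% |
|---|---|---|---|---|
| Streamed nothing | 0% | 4.4 | 8.8 | 17.6 |
| 7 full days | 7.7% | 4.0 | 8.0 | 16.1 |
| 6 weeks at 88% | 40.6% | 2.4 | 4.7 | 9.5 |
| 6 full weeks | 46.2% | 2.1 | 4.2 | 8.4 |
| 13 weeks at 88%, missed assessment only | 88% | 0.0 | 0.0 | 0.0 |
| 13 full weeks, missed assessment only | 100% | −0.6 | −1.2 | −2.4 |

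Entries are percentage points by which the restricted figure exceeds the all-included figure. Two worked cells: 0.20 × (0.88 − 0) = 17.6 points, so the all-included mean is 70.4%; 0.05 × (0.88 − 0.462) = 2.1 points, so it is 85.9%. When excluded patients left early or barely streamed, the range is 2.1 to 17.6 points.

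**4. Direction for other outcomes.** The drop-out rate would be understated. Support time and problem counts would also be understated if leavers had more trouble than stayers, which the document does not say.

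**The case against.** The strongest reply is that the rule was never meant for phase one. It asks for a clinical assessment together with streamed data, which is the pair needed to relate sensor measures to clinical measures in Data Analyses, Phase Two. Drop-out rate and recruitment bias cannot sensibly be computed on week-7 completers, and Results reports recruitment on 1164 applicants, 342 invited and 300 included. An article also condenses the full protocol.

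Much of this stands. A reader might infer that every primary feasibility result will describe survivors only. The documents do not support that: drop-outs must in practice be counted among all included patients, and support time, problem types and drop-outs do not depend on the streaming clock. The exposure is to the three compliance measures, for which no other denominator is named. The intended scope may be narrower, but the text does not say so. The rule closes a section that also covers support and logistics data, and the analysis section speaks of analyses in both phases. It is a stated rule, so the point does not rest on detail left to another document.

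A reader might also take 14% as the observed loss, because Table 1 shows 258 participants against 300 inclusions. The gap is 300 − 258 = 42, but 342 − 300 is also 42, and Table 1 leaves out refusers as well as drop-outs. The same non-participants may have been subtracted twice. Nothing ties the 42 to this rule, so no single figure should be built on it. Nor is the pilot's 88% stated to concern retained patients.

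Two further demands go too far. Minimum valid hours and a window around the assessment are analysis-plan detail. Starting the clock at device delivery would count shipping and set-up as non-compliance, which changes the question being answered.

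**Conclusion.** The concern holds for the compliance outcomes. Followed as written, the rule selects on retention and on streaming itself, and it contradicts the use of drop-outs as a primary outcome. The direction is clear when excluded patients left before week 7 or hardly streamed, and retained patients exceed 46.2% and 7.7% respectively. At 88% in retained patients, the bias vanishes only if excluded patients streamed throughout and merely missed the assessment.

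The size is unknown. About 2 to 18 points rests on three assumptions: 88% in retained patients, 5% to 20% excluded, and leavers streaming between nothing and six full weeks. Phase one is descriptive and has no pass mark, so no formal test is affected. The compliance figure is nevertheless part of the primary aim and informs phase two, so the rule should be corrected before the results are reported.

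**What to change.** - State that all phase-one feasibility and compliance outcomes are computed on all 300 included patients.
- For "the percentage of time that sensor data were streamed during the follow-up period", use a fixed 13-week denominator. Count time after stopping as not streamed, and give included patients who never stream 0%.
- Report phase-one compliance in the set defined by the current rule only as a secondary figure, labelled as such.
- Confine the current rule to analyses that relate sensor data to clinical measures.

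The cost is a change of wording and descriptive tables on a wider set of patients. No new data collection is needed. The downside is that the headline compliance figure will probably be less favourable.

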#### Phase Two

The potential for the data to answer clinically relevant research questions will be explored. First, we aim to extract a limited set of outcomes, including: the number, diversity, and performance of physical activities; specific activities (eg, standing, walking, sitting); response fluctuations in relation to drug treatment; and specific motor symptoms (eg, tremor, gait freezing, shuffling, falls).

Additionally, we aim to explore how these outcomes are related to clinical assessments, and to self-monitoring during follow-up (including timing of medication intake and fall incidents). Finally, we aim to extract patterns of disease progression, assess the recognition of disease profiles based on reported symptoms and progression patterns, and address the effect of medication intake on symptoms. In both phases, analyses will be performed using specialized algorithms (when necessary) developed within the Matlab platform, with additional statistical analyses using the R software package.

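### The single analysis-entry rule requires the clinical visit even for phase-two analyses that use only sensor and app data

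*Protocol article*

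**What the plan says.** The entry rule stands at the end of Data Collection and Management in the protocol article: "Patients that complete the clinical assessment and stream data for more than seven days will have their data included in further analyses". It joins two conditions, is not tied to any type of analysis, and is the only such rule in the article.

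Study Design fixes when the first condition can be met:

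- There is one visit: "participants will attend a one-time consultation, during which a detailed clinical assessment will be performed".
- Its timing: "This clinical assessment will take place in week 7, or later during the follow-up period".
- The observation period: "Follow-up will occur after 3 months (13 weeks), starting from the moment the first data are streamed to the server".
- Phase two follows the same pattern. Its clinical and device data collection, "as well as the follow-up period, will be identical to phase one".

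The Phase Two part of Data Analyses starts with extracting activities, motor symptoms and response fluctuations from the sensor signals. These outcomes are then to be related to the clinical assessments and also "to self-monitoring during follow-up (including timing of medication intake and fall incidents". A later aim is to "address the effect of medication intake on symptoms". According to the Abstract, medication intake and falls are reported by patients in the smartphone app, so those two analyses do not depend on the visit.

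**The concern.** The streaming condition implies that just over a week of data is enough for a patient to contribute. The visit condition overrides it, because the visit cannot take place until the seventh week. For about the first half of follow-up a patient can hold enough sensor data and still be unable to qualify. A patient who misses the one visit never qualifies, however much was streamed.

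For comparisons of sensor outcomes with clinical scores this is unavoidable: without a score there is nothing to compare. For analyses built on sensor signals and app self-reports alone, the visit adds nothing to the calculation, yet its absence removes the patient. Two things are at stake. The sensor-only results describe patients who attended a visit rather than patients who streamed, and some precision is lost. The first matters more, because the article keeps its entry criteria broad to capture varied patients and names selection bias as a challenge in the Discussion. This rule adds a further selection at the analysis stage, where it can be avoided.

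**Working it through.** The article states no figure for this point, so there is none to reproduce. The check has three parts.

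**1. The schedule (all inputs from Study Design and the entry rule)**

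- Follow-up: 13 × 7 = 91 days.
- Week 7 opens on day 6 × 7 + 1 = 43.
- More than seven days of streaming is first reached on day 8.
- Days on which the streaming condition can be met but the assessment condition cannot: day 8 to day 42, that is 42 − 8 + 1 = 35 days.
- Most data held by someone who leaves before week 7: 42 of 91 days, 42/91 = 46%. In hours this is 42 × 24 = 1,008 with uninterrupted streaming. At the pilot's 88% streaming compliance it would be 0.88 × 1,008 ≈ 887.

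Applying the rule as written:

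| Patient | Days streamed | Assessment | Included? |
|---|---|---|---|
| Leaves on day 42 | up to 42 | not yet possible | no |
| Streams all 13 weeks, misses the visit | up to 91 | missing | no |
| Streams eight days, attends the visit | 8 | done | yes |

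**2. Which phase-two analyses need the score**

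- Needs it: the relation of sensor outcomes to clinical assessments.
- Can be done without it: extraction of activities and motor symptoms; the relation of these to self-reported medication times and falls; the effect of medication intake on symptoms.

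**3. Size in phase two**

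From the article: 700 additional patients and 13 weeks, so 700 × 13 = 9,100 planned patient-weeks. Assumed, because the article gives no drop-out rate: 5%, 10% or 14% of patients leave; leaving time is uniform over 0 to 13 weeks; visit time is uniform over 6 to 13 elapsed weeks and independent of leaving.

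Share of leavers with more than one week of data and no visit:

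- leaving between elapsed weeks 1 and 6: 5/13
- leaving between elapsed weeks 6 and 13 but before the visit: (7/13) × 1/2 = 3.5/13
- total: 8.5/13 = 0.65

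Mean time on study of these patients: the first group averages 3.5 weeks and the second 6 + 7/3 = 8.33 weeks, so (5 × 3.5 + 3.5 × 8.33)/8.5 ≈ 5.5 weeks.

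| Leavers | Patients left out | Patient-weeks left out | Share of 9,100 |
|---|---|---|---|
| 5% | 700 × 0.05 × 0.65 ≈ 23 | about 125 | 1.4% |
| 10% | 700 × 0.10 × 0.65 ≈ 46 | about 250 | 2.7% |
| 14% | 700 × 0.14 × 0.65 ≈ 64 | about 350 | 3.8% |

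The shares use the rounded patient-weeks; unrounded, the last two are 2.8% and 3.9%.

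If a further 5% stay but miss the visit: 700 × 0.05 = 35 patients and at most 35 × 13 = 455 patient-weeks, 455/9,100 = 5%.

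Effect on a standard error, counting each patient once: √(700/677) = 1.017 for 23 left out and √(700/636) = 1.049 for 64, so about 1.7% to 4.9% wider.

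**The case against.** The strongest defence is that phase two is exploratory and built around the sensor-clinical link. The Abstract says that summary statistics from the raw signals will be compared with clinical outcomes, and the extraction step supplies the measures for that comparison. One common complete-case set for linked steps is a defensible choice, and detailed analysis sets are often left to a fuller document. The loss is also small on the figures above, and every rate in them is assumed.

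Much of this stands. It limits the importance of the point but does not remove it. The article does not leave the matter open: it states a rule, and the rule as stated reaches analyses that do not use the visit.

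A reader might infer more than the article supports:

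- *That the data are discarded.* The rule concerns inclusion in analyses. It mentions neither deletion nor the algorithm database, which is described as a separate aim.
- *That only patients who stayed past week 7 remain.* The visit may take place in week 7 itself, and what counts is attending it. Someone with eight days of streaming who attended is included.
- *That those left out are frailer or less engaged.* This is plausible, but the article has no data on it.
- *That phase-one drop-out and compliance are computed after early leavers are removed.* That would be more serious, since those outcomes include "the total hours of sensor data collected per participant, the number of compliant days, and the percentage of time that sensor data were streamed". But the rule does not say which analyses it governs or mention phase-one feasibility, so the article does not establish this.

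**Conclusion.** The point holds in a limited form. Followed as written, the rule leaves out patients with usable sensor and app data from phase-two analyses that need no clinical score, and so conditions those results on attending one visit in week 7 or later. This follows from the entry rule and the visit schedule and needs no assumption about drop-out.

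The size does rest on assumptions. With 5% to 14% leavers and uniform leaving and visit times, about 23 to 64 of 700 patients are left out, or about 1.4% to 3.8% of planned patient-weeks, plus up to 5% more if 5% miss the visit. The loss of precision is modest. The direction and size of any bias cannot be worked out from the article. This is an inexpensive improvement to a stated rule and does not threaten the study as a whole.

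**What to change.** Replace the single rule with two sets, chosen by what each analysis uses:

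- **Sensor-versus-clinical comparisons:** assessment completed and more than seven days streamed, as now.
- **Analyses using only sensor and app self-report data:** every patient with more than seven days streamed, whether or not the visit took place, with a flag for visit done or not done.

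Report n for each set. The same edit can name the analyses that each set governs, which would also settle whether phase-one outcomes are affected.

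The cost is a short change of wording and no new data collection. The one drawback is that n will differ between analyses; reporting n per set and using the visit flag to compare the two groups makes that difference visible.

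### The entry rule for analysis has no stated scope; applied as written to phase one, it selects on the streaming and retention that phase one is meant to measure

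*Protocol article*

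**What the plan says.** The Introduction gives feasibility and compliance as the main purpose: "The primary aim of the Parkinson@Home study is to evaluate the feasibility and patient compliance of using wearable sensors to collect data for at least" three months.

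Under Data Analyses, Phase One, the feasibility outcomes open with "the primary outcomes will include the total support time per participant, the number and rate of drop-outs". The compliance outcomes are "the total hours of sensor data collected per participant, the number of compliant days, and the percentage of time that sensor data were streamed", measured over the follow-up period. No analysis population is named for any of them.

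The last sentence of Data Collection and Management, immediately before Data Analyses, sets a single entry rule: "Patients that complete the clinical assessment and stream data for more than seven days will have their data included in further analyses". It is not tied to a phase or to a type of analysis.

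Study Design fixes the timing. On the assessment: "This clinical assessment will take place in week 7, or later during the follow-up period". On the clock: "Follow-up will occur after 3 months (13 weeks), starting from the moment the first data are streamed to the server". It also says that the phase-two devices and raw-data strategies will be chosen after the phase-one data have been evaluated.

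**The concern.** The rule has two conditions, and each is tied to a phase-one outcome. The streaming condition is a threshold on the quantity that hours collected, compliant days and percentage of time streamed all measure, so it cuts off the lower tail of those distributions. The assessment condition requires a patient to be available until at least week 7, so anyone who leaves earlier is removed from a set that would be used to report "the number and rate of drop-outs".

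Compliance would then be described among patients already selected for some compliance, and drop-out among patients who had stayed for about half of follow-up. This touches the primary aim, and the phase-one evaluation informs the choice of devices and data strategies for a further 700 patients.

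**Working it through.** **Figures in the article.** The article states no compliance or drop-out figure that depends on the rule. The nearest figure that can be recomputed is the phase-one participation rate in Results: 300/342 = 87.7%, as stated.

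**How strong each condition is.** Follow-up is 13 weeks, or 91 days.
- Streaming condition: 7/91 = 7.7% of follow-up.
- Assessment condition: reaching the start or end of week 7 is 6/13 = 46% to 7/13 = 54% of follow-up. This is the stronger filter for retention.

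**Compliance.** Let e be the share excluded, k the mean compliance of kept patients and x that of excluded patients.
- All-included mean = (1 − e) × k + e × x
- Overstatement = e × (k − x), which is positive whenever x is below k

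Neither e nor x is in the document. For illustration, k = 88% is the pilot's streaming compliance (20 patients, four weeks; Study Design). The value e = 14% is (300 − 258)/300, the gap between the inclusions and the Table 1 participants in Results, used only as a convenient value.

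| Assumed x | All-included mean | Overstatement |
|---|---|---|
| 7.7% (7 of 91 days) | 0.86 × 88 + 0.14 × 7.7 = 76.8% | 11.2 points |
| 50% | 0.86 × 88 + 0.14 × 50 = 82.7% | 5.3 points |
| 80% | 0.86 × 88 + 0.14 × 80 = 86.9% | 1.1 points |

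Varying e with x held at 7.7%:
- 5% excluded: 0.95 × 88 + 0.05 × 7.7 = 84.0%
- 20% excluded: 0.80 × 88 + 0.20 × 7.7 = 71.9%

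**Drop-out.** With N = 300, D drop-outs and a share s of them leaving before they meet the rule, the rate in the restricted set is (D − sD)/(N − sD). Both D and s are assumptions.

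| D (true rate) | s = 25% | s = 50% | s = 75% | s = 100% |
|---|---|---|---|---|
| 30 (10.0%) | 7.7% | 5.3% | 2.7% | 0% |
| 42 (14.0%) | 10.9% | 7.5% | 3.9% | 0% |
| 60 (20.0%) | 15.8% | 11.1% | 5.9% | 0% |

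For D = 42 and s = 50%: (42 − 21)/(300 − 21) = 21/279 = 7.5%.

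A constant hazard gives a similar picture. If 14% leave over 13 weeks, 1 − 0.86^(6/13) = 6.7% leave in the first six, before any assessment. The rate among those remaining is (14 − 6.7)/(100 − 6.7) = 7.8%. For a true 20%, the figures are 9.8% early and 11.3% among those remaining.

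**The case against.** The best defence is that the rule was meant only for comparing sensor measures with clinical measures. It requires a completed clinical assessment, which has no role in counting hours streamed. A drop-out count confined to patients who stayed would also defeat its own purpose, and Results treats drop-outs as an identified group outside the participants. This is a plausible account of the intention, and it makes the drop-out limb the weaker of the two. The text does not say it, however. No sentence exempts the phase-one outcomes or states that they use all 300 included patients.

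A reader might go further and infer three things that the document does not support:
- **That the bias is certain.** It follows only if the rule is applied literally to phase one, and for compliance only if excluded patients streamed less than kept ones.
- **That the overstatement is at least 11 points.** That figure assigns every excluded patient 7 days or fewer. A patient excluded only for lacking the assessment may have streamed for much longer, and the overstatement then shrinks to 5.3 or 1.1 points in the table above.
- **That 14% is an exclusion or drop-out rate, or that Table 1 shows the rule in use.** The difference 300 − 258 = 42 equals 342 − 300 = 42, so its meaning is unclear, and it was reported before phase-one follow-up ended.

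It can also be said that phase one is descriptive, with no stated compliance threshold, and that support time and problem types feed the same evaluation. That limits the effect on decisions. It does not remove the need for the main descriptive figures to refer to the patients actually included.

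Nor is this a detail left to an analysis plan that is not shown: the article does state the rule, and states it without limit.

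**Conclusion.** The point holds as a conditional one. The direction is clear if the rule is applied to phase one: compliance is overstated when excluded patients streamed less than kept ones, and drop-out is understated when anyone leaves before meeting the rule. Drop-outs after the assessment would still be counted, so the drop-out rate is not necessarily driven to zero.

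The size cannot be derived from the document. On the illustrative values, a reported 88% corresponds to about 77% to 83% among all included patients as the excluded patients' streaming goes from 7 days to half the time. These are examples that rest on the assumed 14% and on the pilot's 88%, and neither end is a limit. Because the primary aim is affected and the correction is simple, the change should be made.

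**What to change.** Limit the entry rule to the analyses that relate sensor data to the clinical assessment. Then state under Data Analyses, Phase One, that compliance and drop-out use all 300 included patients, with 13 weeks as the denominator and time without streaming counted as zero.

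The 13-week denominator largely spells out what the article implies, but it makes clear that patients who leave early keep the full denominator. Patients who never stream need explicit mention, because the follow-up clock starts with the first data received and so never starts for them. They should count as zero compliance.

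The figure among patients who meet the entry rule can be reported as a secondary description. The cost is one or two sentences and no new data. The downside is a less favourable compliance figure.
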